#### Control condition: support as usual plus advice on potential supportive resources

Students in the control condition get support as usual plus advice on potential supportive resources. At Mbo Utrecht, students in this condition meet on a regular basis with their own student service provider who advices them about regular supportive resources that are in place at the educational institute. At the Hanze University, there are no student service providers with comparable tasks, therefore an educational staff member has been trained on giving advice to students about potential supportive resources. In three face-to-face meetings and two consults by phone, this staff member provides the students in this condition with:
Information on formal and informal support opportunities inside and outside the school (e.g., contact with a fellow student or a family member or a consult with a disability support service member or a psychologist)Basic information on studying with mental health problems (e.g., rights and responsibilities of students, students’ stories of studying with mental health problems)Information on assistive technology and sources

Subsequently, the student decides for himself whether he follows the advice of the staff member. It is recorded by the student service providers (at Mbo Utrecht) and the staff member (at the Hanze university) how many meetings take place and what kind of support is offered.

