With respect to the primary outcome, remaining at school, we will compare the number of students who remained in education or graduated in the experimental and the control condition at T2. Logistic regression models will be conducted to test the differences between the experimental and control condition. In addition, the differences in scores on the secondary outcomes, study success and student satisfaction, will be examined for T0 to T2 using chi squares or repeated measures of variance with the ANOVA test using 95% confidence levels, respectively. Furthermore, the differences between the two conditions on number and duration of contacts with the SEd specialist, the trained staff member or students service provider; the number of study skills where the students need support with and the number of resources needed or used when studying, student general self-efficacy levels and the working alliance with the professional, will be calculated using the ANOVA test with 95% confidence levels. Moreover, to test whether outcomes are similar for students from both educational institutions, sensitivity analyses will be performed excluding students from the institute for intermediate vocational education.

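### Re-running the analysis without the vocational institute is called a test of similarity between institutes, but it neither estimates nor tests a difference between them

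*Protocol article*

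**What the plan says.** Under Proposed analyses, the primary outcome is analysed in all students: "Logistic regression models will be conducted to test the differences between the experimental and control condition". No institute term or condition-by-institute term is mentioned. The section then gives one analysis of whether results agree across institutes: "to test whether outcomes are similar for students from both educational institutions, sensitivity analyses will be performed excluding students from the institute"; the institute left out is the vocational one. The aim is a test of similarity, and the method is an exclusion.

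The Control condition section describes different arrangements at the two sites. At the vocational institute, "students in this condition meet on a regular basis with their own student service provider who advices them about regular supportive resources" already in place there, and no number of meetings is given. At the university, "there are no student service providers with comparable tasks, therefore an educational staff member has been trained on giving advice to students", and the contact is specified: "In three face-to-face meetings and two consults by phone, this staff member provides the students in this condition with" a listed set of information.

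Three other statements bear on the point. Study procedures says that randomisation is done separately at each institute. The Control condition and Measurements sections say that the number, duration and kind of support contacts are recorded. Process evaluation says that this evaluation is carried out for each site separately; no such by-site statement is made for the trial outcomes.

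**The concern.** A test of similarity needs an estimate from each institute and a comparison of the two. The exclusion supplies one of the two estimates, and the only thing to set it against is a pooled estimate built partly from the same students. This invites two errors:

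- **False alarm.** The subset is smaller, so significance can be lost when the effect is the same everywhere. That loss could be taken to mean that the institutes differ.
- **False reassurance.** The two results overlap, so they look more alike than the two institutes are.

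Institute is not an idle factor here. The intervention is compared with the student's existing provider at one site and with a specially trained staff member on a set contact schedule at the other. Readers will want to know whether the effect is seen against both. The institute whose estimate is not stated is the one that the exclusion removes.

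**Working it through.** The plan gives no figure for this analysis, so there is none to reproduce. The steps below show what the exclusion measures and how it behaves.

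**Inputs.** Power of 80% and alpha of 0.05 come from Sample size calculation. The article does not state whether alpha is one- or two-sided; two-sided is assumed here. The share of students from the university, w, is not given; 0.5 is assumed, with a range of 0.3 to 0.7. Effects are on a standardised scale with a normal approximation.

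**1. What is compared.** Let U and V be the university and vocational effect estimates. The pooled estimate is roughly P = wU + (1 − w)V. Then U − P = (1 − w)(U − V). At w = 0.5, setting the university result beside the pooled one shows half of the between-institute difference. The two estimates correlate at √w = √0.5 = 0.71.

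**2. Identical true effects, full-sample power 80%.** The expected full-sample z is 1.960 + 0.842 = 2.802. In the university subset it is 2.802 × √w, and subset power is Φ(2.802√w − 1.960), where Φ is the standard normal distribution function. The probability that both results are significant comes from simulating the two correlated z-values. The share of significant results that is lost is 1 − P(both significant)/0.80.

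| University share w | Expected z in subset | Subset power | P(both significant) | Significant results lost |
|---|---|---|---|---|
| 0.7 | 2.344 | 0.65 | 0.627 | 1 − 0.627/0.80 = 22% |
| 0.5 | 1.981 | 0.51 | 0.487 | 1 − 0.487/0.80 = 39% |
| 0.3 | 1.534 | 0.34 | 0.318 | 1 − 0.318/0.80 = 60% |

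At w = 0.5 and full-sample power of only 50%, subset power is 28% and 51% of significant results are lost.

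**3. A real difference.** Suppose the effect is 0.75 at the university and 0.25 at the vocational institute, with w = 0.5. The full-sample and university-only significance verdicts agree in 79% of simulated trials with 102 students and in 86% with 140. A threefold difference would usually pass unnoticed.

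**4. The direct contrast.** The contrast U − V has standard error √(2/n_U + 2/n_V), where n_U and n_V are the numbers per condition in each institute.

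- 102 students, w = 0.5: n_U = n_V = 25.5, so the standard error is √(4/25.5) = 0.396. For true effects of 0.5 and 0, the expected z is 0.5/0.396 = 1.26 and power is 24%.
- 140 students, w = 0.5: n_U = n_V = 35, so the standard error is √(4/35) = 0.338. The expected z is 1.48 and power is 32%.
- Over w from 0.3 to 0.7 and both totals, power is 21% to 32%.

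This contrast signals a difference wrongly in 5% of trials when effects are equal, whatever the split. Its power is low, so its confidence interval is more informative than its p-value.

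**The case against.** Four points can be made for the plan.

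**The vocational result is not withheld.** A reader might infer that it will never be shown. The article does not say that; it only does not list that estimate, and by-institute tables are often left to a fuller plan. Step 1 also shows that V can be recovered approximately from P and U. This stands. The mismatch remains, because the article itself names the exclusion as the way to test similarity.

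**The differing control condition is not in itself a defect of the pooled comparison.** A reader might infer that pooling two comparators biases the result. The documents do not support this. Randomisation is within institute, so the pooled effect is an average over two local forms of usual support. The article describes both forms openly, records the contacts and evaluates each site separately. What stands is that institute-specific effects are needed to interpret that average.

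**The loss figures depend on how the check is read.** The article does not say that it will be judged by significant versus non-significant; comparing estimates and intervals is equally compatible with the text. The 22% to 60% range is therefore conditional, not an expected error rate. Nor should the 15% and 8% dropout figures in the Background be turned into retention rates for this purpose: they are five-year rates in students with and without mental health problems, not a treatment effect at 12 months.

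**A direct test would be weak.** This is correct (step 4). It argues for reporting estimates with intervals, not for keeping a procedure that contains no test of a difference.

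**Conclusion.** The point holds as a mismatch between a stated aim and a stated method. The exclusion is a legitimate robustness check on the pooled result, but it cannot serve as the test of similarity that the sentence makes it.

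If read by significance, it would turn 39% of significant results non-significant with no true difference between institutes, at 80% full-sample power and a 50:50 split (22% to 60% over the assumed range of shares). These figures rest on an assumed split, a two-sided 0.05 level and a normal approximation.

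The primary comparison and its error rate are unaffected. The correction should be made, but it concerns a supporting analysis.

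**What to change.** Reword the sentence under Proposed analyses along these lines:

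- Excluding the vocational institute is a robustness check on the pooled result.
- Similarity is assessed by reporting the condition effect with 95% confidence interval in each institute, and the between-institute difference in effect with 95% confidence interval.
- The scale suits the outcome. For remaining at school, use the ratio of odds ratios from the condition-by-institute term of the logistic model, or risk differences by institute and their difference, calculated separately. These are two different scales and can disagree, so name one in advance. For continuous outcomes such as grade point average or satisfaction, use the difference in mean differences.
- This contrast has low power, and a non-significant result is not taken as evidence of similarity.
- The institute-specific effects are interpreted alongside the recorded number, duration and kind of support contacts at each site, because the control support differs.

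Randomisation is already separate by institute, so no new data are needed. The cost is a little extra analysis and institute-level estimates that will be imprecise. If few students leave school, the logistic interaction may also be unstable within an institute.

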### Process evaluation

The process evaluation focuses on five main questions recommended by the guideline for process evaluation of Movisie (the Dutch national knowledge institute in the social domain [57]). These five main questions are: 1) Was the intervention conducted as planned? 2) Wat is the reach of the intervention? 3) What are the experiences of participants and support staff? 4) What are the success and failure factors of the intervention? 5) What recommendations can be made based on the process evaluation to improve the intervention? The process evaluation will be conducted for both sites separately (i.e., Groningen and Utrecht). Table 2 shows how the five process evaluation questions will be addressed in the present study.

**Table 2 Tab2:** Overview of instruments used to address the five process evaluation questions

Main topic	Experimental condition	Control condition
	*Instrument (timing)*	*Instrument (timing)*
1. Fidelity	SEd fidelity questionnaire (T1)	Evaluation checklist (after each meeting)
2. Reach	Registration information: - number of students who contacted the research team to participate in this study - number of students who eventually participated in the trial - recruitment period - number of drop-outs	Registration information: - number of students who contacted the research team to participate in this study - number of students who eventually participated in the trial - recruitment period - number of drop-outs
3a. Students’ experiences	- Interview (within one month post-intervention) - Drop-out interview (within one month after drop-out) - Focus group (T2)	- Questionnaire (T2) - Drop-out interview (within one month after drop-out)
3b. Experiences of support staff	- Evaluation checklist (after each meeting) - Interview (T2)	- Evaluation checklist (after each meeting) - Interview (T2)
4. Succes and failure factors (including essential components^a^)	Based on the outcomes of 1–3.b	Based on the outcomes of 1–3.b
5. Recommendations	Based on the outcomes of 1–4	Based on the outcomes of 1–4

^a^Part of the evaluation of the experimental condition

#### Fidelity

To assess fidelity, the SEd specialists will be interviewed once about one of their –randomly chosen- students, using a SEd fidelity questionnaire which is based on the Psychiatric Rehabilitation (PR) fidelity questionnaire used in a RCT on PR [58, 59]. The PR fidelity questionnaire was originally developed in Dutch and is aimed at four life areas: living, working, learning and socializing. For our SEd fidelity questionnaire we only used the questions about ‘learning’. With this questionnaire, the degree to which the SEd intervention is adhered to, will be scored. A score of 70% or higher will be regarded as sufficient fidelity [60].

The staff member in the control condition will fill out a short (self-constructed) evaluation checklist on which they indicate how they experienced the communication with the student, what they have discussed and, what the structure of the meeting was.

#### Reach

To assess the reach of the study the following data will be recorded: the number of students who contacted the research team to participate in this study, the number of students who eventually participated in the trial, the recruitment period and the number of students who drop out early.

#### Students’ experiences with the interventions

Students in the experimental condition will be interviewed by the researcher about their experiences with the SEd-intervention (semi-structured interview). Interviews will be scheduled within one month post-intervention. The themes covered in the interview are (1) benefits of the intervention (e.g. ‘Did the support help you to reduce the barriers that you experience with studying due to your mental health problems?’), (2) aspects concerning the structure of the intervention (e.g. ‘What did you think of the duration of the appointments?’), (3) materials (e.g. ‘Did you make use of the worksheets? If so, in what way/how did you use them?’), (4) the SEd-specialist (e.g. ‘What did you think of the SEd-specialist?’) and, (5) success- and failure factors, including essential components. (e.g. Students will be asked to indicate for each of the five principles of SEd whether they recognize the principle and which of the principles they regarded as most helpful). Students who drop-out before the study is closed will also be interviewed. This interview covers the same topics as the regular interview, but with an additional topic on reasons for drop-out.

Furthermore, focus groups will be organized at T2 at both sites with students who participated in the experimental condition and thus received SEd. The goal of the focus group is to get more in-depth insight into the essential components of the SEd intervention, as through the interaction with others, students can nuance their thoughts about the intervention. Results from the interviews that took place within one month after ending the support, will be used to determine the content of the focus groups. We plan to conduct two focus groups with six to eight students, one at each site, each focus group will last one-and-a-half to two hours. The focus group will be led by the researcher and a research assistant.

Students’ experiences with the control condition will be examined using a self-report questionnaire (self-constructed) administered at T2. The questionnaire consists of open-ended and closed-ended questions and includes the following topics: (1) benefits of support (e.g., ‘Did the support help you to reduce the barriers that you experience with studying due to your mental health problems?’ Students rate their level of agreement on a scale from 1 = strongly disagree, to 5 = strongly agree), (2) aspects concerning the structure of the support (i.e., ‘What do you think of the number of contact moments you had with the staff member?’. Answer options: 1 = too little, 2 = about right, 3 = too much), (3) material (i.e., ‘The brochure was clear’; students rate their level of agreement on a scale from 1 = strongly disagree, to 5 = strongly agree), (4) the staff member (e.g., ‘What did you think of the staff member?’), and, (5) success and failure factors (e.g., ‘Suppose we start offering this support to students from other colleges or universities as well. What do you think is really important to keep as it currently is?’). Students who drop-out before the study is closed will additionally be interviewed about reasons for drop-out.

#### Experiences of support staff

After each meeting with a student, the SEd specialists will fill out a short (self-constructed) evaluation checklist on which they can indicate how they experienced the communication with the student, which of the five steps of the SEd intervention they have discussed with the student, what they have discussed and what the structure of the meeting was. At T2, the SEd specialists will be interviewed about their experiences with providing the support including what they regard as the essential components. The themes covered in the interview are (1) general information (e.g., ‘How many students did you support using the SEd-intervention?’), (2) support (e.g., ‘Did you feel sufficiently competent to provide the SEd-intervention?’), (3) material (e.g., ‘How did you like working with the worksheets?’), (4) aspects concerning the structure of the intervention (e.g., ‘What did you think of the duration of the appointments?’), (5) benefits of the intervention for students (e.g., ‘What difference did you notice during the SEd-intervention regarding the students’ satisfaction at school?’) and, (6) success- and failure factors, including essential components (e.g., ‘Suppose we start offering this support to students from other colleges as well. What do you think is really important to keep as it currently is?’). The staff members in the control condition will also be interviewed about their experiences at T2 in which the same themes will be covered as in the interview with the SEd specialist, except of course for the question about the essential components of the intervention.

Together, the results of this process evaluation may provide indications for possible improvements in the contents of the SEd intervention or in the implementation of the intervention. In addition, the qualitative results can provide context for the interpretation of the quantitative findings.

### Data analysis and data management

The interviews and focus groups will be audio-taped and transcribed. Subsequently, the data will be analyzed using content analysis techniques [61]. All data gathered in this study will be handled confidentially in compliance with the Dutch Personal Data Protection Act (Wet Bescherming Persoonsgegevens; WBP). All data will be stored and locked at the Hanze University of Applied Sciences Groningen and will be destroyed ten years after finishing the study.

## Discussion

This study will be the first RCT worldwide on the effect of SEd on remaining at school, study success and student satisfaction among students with mental health problems. If the results of this study show positive effects of the SEd intervention on these outcomes, the intervention will be disseminated to mental health and educational organizations, policy makers and to student-, client- and family organizations. In addition, it will be submitted to the database ‘Effective interventions’ of the NJI (Dutch Youth Institute). In this way, also professionals in the field of education and of mental health who did not participate in the project have an effective intervention available to them to support the increasing number of students with mental health problems to remain at school. The use of a mixed-methods design hopefully results in a comprehensive, thorough evaluation of the SEd intervention.

Conducting a RCT brings along a few difficulties. Within the project team, knowledge about RCTs is available and the two sites at which the RCT will be conducted, have experience working with the SEd intervention before. Moreover, an independent advisory board, consisting of students with mental health problems, researchers, and professionals from education and mental health, has been installed at the beginning of the project. This advisory board provides asked and unasked feedback during all phases of the research project. Advisory board meetings will be scheduled twice a year, at which the progress of the study will be discussed, including the trial conduct. Finally, the total procedure (registration, randomization, filling out the questionnaire and the first contact with the Supported Education specialist or the trained staff member in the control condition) has been tested with a student which resulted in a few minor adjustments. For example, the question about receiving treatment has been adjusted so it is clear that treatment for mental health problems is meant and a technical problem with uploading the overview of study progress has been resolved.

A bottleneck of many RCTs is the low influx of participants [62–64]. Therefore, in this study we will be attentive on the inclusion speed: can a sufficient influx of students be expected per site; is there still a willingness to participate at the various levels of the organization, and are disturbing factors for the project expected (e.g. a reorganization)? In addition, we will closely monitor the influx of students during the recruitment phase by evaluating monthly if recruitment rates are on track, in order to identify potential problems in time and initiate additional actions to boost inclusion.

In order to recruit a sufficient number of students, we asked the advisory board to advise us about relevant recruitment strategies. The recruitment strategies that were mentioned like posts on the internal website of the schools and on social media, posters, information brochures and personal contact with educational professionals will be used in the study.

To increase the chance that we reach a sufficient number of students for our study, we decided that the inclusion period of students is six months. Consequently, there will be differences at baseline being the point in the school year the student is enrolled in the study. However, we expect these differences to be the same in the experimental and control condition. We will report this information and if necessary, we will take it into account during the data analysis.

In addition, the attrition of participants can be a threat to studies in which follow-up measurements are used [63, 65]. In the informed consent form of our study, students give permission to collect information about their school progress (drop-out, grades, and course credits) from the school’s administration system also in case they drop-out of the study. In this way, complete and objective data regarding our primary outcome (remaining in school) and a part of our secondary outcomes (study success) are guaranteed.

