### Participants

Study participants are students with mental health problems who want to complete their current education studying at Mbo Utrecht, which is an educational institute that provides post-secondary vocational education, or at the Hanze University of Applied Sciences Groningen, an educational institute for higher professional education. They will be recruited through personal contact with educational professionals, information brochures (see Additional file 1), posts on the internal website of the schools, posters and social media. Inclusion criteria are:
having a mental health condition (e.g. depression, anxiety disorder, bipolar disorder, psychosis, ADHD) for which the student has received a formal diagnosis or the student experiences symptoms for at least 6 months, and;receiving treatment for mental health problems or having received treatment in the past, and;being at least 16 years of age, and;following regular post-secondary vocational education in Utrecht; or higher education in Groningen, and;expressing the need for extra support to remain at school.

Exclusion criteria are:
not fluently speaking and reading in Dutch, or;the need for extra support is only expressed by others than the student, or;unable to give informed consent, or;less than six months to go before graduation, or;has received SEd services in the past

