### Study procedures

We adhere to the SPIRIT 2013 guidelines [40], the checklist is provided in the Additional file 2.

Students who heard about the study through one of the recruitment strategies and are interested in participation, contact the research team by e-mail. A data coordinator will check the inclusion criteria and will then send a link to an online questionnaire which starts with information about the study and the question to fill out an informed consent form. In the informed consent (see Additional file 3), students state that they have been informed about the study and that they participate voluntarily. In addition, they give permission to collect grades and course credits from the school’s administration for the next five years, so we are able to follow the study success of the students after the current project has finished. They also give permission that in case they drop-out of the study, school progress keeps being monitored. Students have the right to withdraw this permission at any moment in time.

After signing the informed consent, the students fill out the baseline-questionnaire. Then, students will receive a student ID number and will be randomized, for both educational institutes separately, by the data coordinator in either the experimental condition (Supported Education-coaching; half of the group of students) or the control condition (support as usual plus advice on potential resources; half of the group of students), using the minimization approach [41] which aims to minimize imbalance between the conditions on specific factors, in our case on gender, age, ethnicity, study year, level of study, the number of credits completed, and level of psychological distress. The condition to which the student is allocated depends on the characteristics of the students that were already enrolled. Students will receive compensation (a gift coupon of 12,50 euro each) for filling in the questionnaires at baseline, 6- and 12-month follow-up. Within this 12-month follow up, each student experiences a critical moment in the educational pipeline: either transitioning to the next year or graduating. In Table 1, the Spirit flow diagram of the study procedure is presented.

**Table 1 Tab1:** SPIRIT flow diagram of the study procedure showing enrolment, interventions, and assessments

	Pre-intervention	Post-intervention (within one month)	6 month follow-up	12 month follow-up
**TIMEPOINT**	**t**_**0**_		***t***_***1***_	***t***_***2***_

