### Proposed analyses

Analyses will be performed according to the intention-to-treat principle and we will control for any variation in observable characteristics between conditions that remained after the minimization procedure that was used to randomize the students into the conditions. Missing values in the questionnaires will be prevented as the questionnaires are administered through an online secure software program (Enalyzer) in which answering to all items is obligated. The main outcome measure (remaining at school) will be insensitive for missing values as this data can be retrieved from the administration offices of the educational institutes. In case of missing data (for example, when a student does not fill in the second or third questionnaire), intention-to-treat analyses will be performed to account for incomplete outcome data [55]. In addition, it will be examined whether the rates of incomplete data differ between the control and experimental condition. To detect any outliers, the median absolute deviation method will be used [56]. Unrealistic outliers (due to e.g. data entry mistake) will be removed. In case of outliers with a realistic value, we will perform the analyses both with and without the outliers and we will report both results.

Descriptive statistics (e.g. frequencies, means and standard deviations) will be provided for all variables. Conventional statistical tests (e.g. regression, chi-square and ANOVA) will be used to address the research questions in accordance with how the data align with the assumptions of these tests (e.g. normality, homogeneity). In case the data are not normally distributed, the non-parametric equivalents will be used (e.g. the Friedman-test, the Mann-Whitney-test and the Wilcoxon signed-rank test).

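### Minimising on an unscaled credit count, with mixed study years and entry dates, leaves study delay balanced hardly better than if credits were left out

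*Protocol article*

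**What the plan says.** Under Study procedures, students "will be randomized, for both educational institutes separately, by the data coordinator", by minimisation, "in our case on gender, age, ethnicity, study year, level of study, the number of credits completed, and level of psychological distress". No scaling of the credit count to programme load, study year or entry date is given, and entry date is not a factor.

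Under Participants, study year is not restricted. The only related exclusion is "less than six months to go before graduation".

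The Discussion states that "we decided that the inclusion period of students is six months" and continues: "Consequently, there will be differences at baseline being the point in the school year the student is enrolled in the study". It adds: "However, we expect these differences to be the same in the experimental and control condition". It promises to report the entry point and to allow for it in the analysis if that proves necessary.

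Under Proposed analyses, "we will control for any variation in observable characteristics between conditions that remained after the minimization procedure". The primary outcome is tested by logistic regression. No measure of study delay is named as a covariate.

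Under Secondary study outcomes, credits are counted per semester when they serve as an outcome. The allocation factor is given no such time base.

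**The concern.** A cumulative credit count is the credits due so far times the share of them earned. The first part depends on study year and entry date; only the second shows whether the student is behind. With an assumed 30 credits per semester, a count of 30 is full progress (30/30) for a first-year who enters after one semester, but one third (30/90) for a second-year who enters after the same semester. The two fall in the same class.

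Study year is already a factor, and minimisation in its usual form balances each factor's margin separately. Balance on year and balance on the raw count do not together give balance on delay. Delay is plausibly what links credits to leaving school: the Background mentions dismissal for not meeting academic standards as one form of dropout. The plan therefore appears to balance a prognostic factor that it may hardly touch.

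**Working it through.** **Inputs.** From the documents: seven factors, separate allocation at two institutes, a six-month window, and 140 students to be included. Assumed, because the documents do not give them: credit load, mix of study years, spread of progress, an even split of 140/2 = 70 per institute, and minimisation on separate margins. The plan states no figure on balance that could be reproduced.

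**Step 1: how far the raw count repeats study year.** Let raw = S × p, with S = 60(y − 1) + 30B. Here y is one of K equally frequent study years, B = 1 with probability 0.5 if the student enters after a semester boundary, and p is the share earned, with mean 0.75 and SD s.

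- Between-year variance: 0.75² × 60² × (K² − 1)/12
- Within-year variance: s² × E[S²] + 0.75² × 225
- K = 4, s = 0.15: between 2531; E[S²] = 15750; within 354 + 127 = 481; share 2531/3012 = 0.84
- K = 2, s = 0.25: between 506; E[S²] = 3150; within 197 + 127 = 323 after rounding; share 506/830 = 0.61

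Over K = 2 to 4 and s = 0.15 to 0.25, study year accounts for 61-84% of the variance of the count. Taken alone, the count explains 13-38% of the variance of p among students with credits due.

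**Step 2: what minimisation achieves.** Biased-coin minimisation (probability 0.8) was simulated at one institute with n = 70, seven factors, 60 credits per year, four equally frequent study years, entry uniform over six months, and pace of study with mean 0.8 and SD 0.1, 0.2 or 0.3. There were 1,500 runs per setting. Relative progress is credits earned divided by credits due at entry. The table gives the SD of the between-arm difference in mean relative progress, in SD units of that measure.

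| Allocation | pace SD 0.1 | 0.2 | 0.3 |
|---|---|---|---|
| Simple randomisation | 0.232 | 0.233 | 0.243 |
| Minimisation, credits left out | 0.237 | 0.235 | 0.242 |
| Raw credits, tertiles | 0.238 | 0.229 | 0.226 |
| Raw credits, 15-credit bins | 0.229 | 0.233 | 0.234 |
| Raw credits, continuous | 0.239 | 0.229 | 0.214 |
| Credits, tertiles within study year | 0.202 | 0.196 | 0.181 |
| Credits relative to credits due, tertiles | 0.168 | 0.161 | 0.164 |

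Theory for simple randomisation gives √(1/35 + 1/35) = 0.239, in line with the first row. The simulation error of each entry is about 0.24/√3000 = 0.004. Raw credits reduce the spread by at most about 12% against leaving credits out (0.214 against 0.242). Scaled credits reduce it by about 30% (for example 0.161 against 0.235). Over two equal institutes, 0.24 becomes 0.24/√2 = 0.17 and 0.165 becomes 0.12.

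**Step 3: what the analysis could recover.** In the model of step 1, among students with credits due, study year and raw credits together explain 45-73% of the variance of p. Adding the entry point raises this to 80-86%.

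**The case against.** The strongest reply is that the analysis can deal with this. The article promises control for remaining differences in observable characteristics, does not limit that to the raw count, and allows entry point to be taken into account. Step 3 shows that these three variables together carry most of the information on delay. Once a covariate is in the model, chance imbalance in it costs only about 1/n of the variance, here 1/140 = 0.7%. This stands as to size. It is not a commitment, however: entry point enters only if judged necessary, without a criterion, and a check on the raw count alone could look balanced while delay is not.

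Secondly, the article does not describe how the factor is coded or which distance the minimisation uses. A per-semester count, or a method that uses factors jointly, would shrink the problem. That also stands; the point rests on the plain reading of the text.

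Thirdly, a reader might infer that the count says nothing about delay once study year is known. That would be wrong. In the model of step 1, raw credits explain 49-71% of the variance of the share earned within year 2 and 87-94% within year 4. Among first-years with credits due, the count is simply 30 times the share. The information is there; allocation on separate margins does not use it.

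A reader might also infer a biased comparison. The documents do not support that: nothing in the allocation favours one arm with respect to delay.

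**Conclusion.** The point holds as a minor improvement. As written, the credit factor leaves chance imbalance in study delay at 0.21-0.24 SD per institute of 70, close to the 0.24 SD seen without it, where a scaled factor would give 0.16-0.17 SD. The harm is chance imbalance and some lost precision on a plausible predictor of the primary outcome. No bias, inflated type I error or quantified loss of power follows.

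The size rests on assumed credit loads, year mix and variation in pace, applied alike to a vocational institute and a university, and on the count being cumulative and balanced on its own margin. That delay is the prognostic part of credits is plausible, but the documents do not show it.

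**What to change.** Under Study procedures, replace the credit count by credits completed divided by credits scheduled for the student's programme up to enrolment. Use two or three classes, plus one for students with none due yet.

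If allocation has already started, leave the minimisation unchanged. Name this share as a prespecified covariate in the logistic regression for the primary outcome under Proposed analyses. Study year, raw credits and entry point together would be an acceptable substitute.

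The cost is one division per student, from the study-progress overview that the Discussion says is uploaded, plus looking up the nominal programme load. The downside is that students with no credits due form a class of their own, within which progress cannot be balanced.
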